### Treatment

Patients with increased pressure determined by the intra-bladder pressure measurements will be treated in compliance with the algorithms for patient management as developed by the WSACS (www.wsacs.org/algorithms.php) [3]. The IAH Assessment Algorithm describes all risk factors that every patient should be screened for upon intensive care unit admission and upon clinical deterioration leading to new organ dysfunction. The intra-bladder pressure will be measured in patients with two or more risk factors for IAH or ACS or in patients who have undergone a liver transplantation. Patients who do not have two or more risk factors at baseline but develop new risk factors during their ICU admission will be followed from that moment onwards. The reason for this is that the occurrence of IAH during intensive care stay is known to be an independent predictor for mortality, whereas presence of IAH at intensive care admission is not [23]. Patients should be enrolled as soon as possible, but at least within 48 hours after meeting the eligibility criteria. The IAH/ACS Management Algorithm provides a decision tree for the follow-up of patients related to the IAP level. The IAH/ACS Medical Management Algorithm provides a stepwise approach of actions to be taken for achieving IAP pressure relief. In short, ICU management will be provided by the attending physicians and may consist of, among others, balanced intravenous fluid administration, correction of hypovolemia, electrolyte disturbances and/or anemia and analgesics.

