### Recruitment and consent

Upon identification of two IAH risk factors, treatment should be initiated in compliance with international guidelines of the WSACS. This implies that the baseline IAP measurement and the first urine sample may have been collected prior to obtaining informed consent from the patient or his/her legal representative. Eligible persons admitted to the ICU who are at risk for developing IAH will be informed about the trial and asked for consent at the ICU. If patients are unconscious or otherwise not able to sign informed consent, their legal representative will be informed about the trial and asked to sign informed consent on behalf of the patient. Upon recovery the patient will be asked to sign final consent. The patient and their legal representative will receive information and a consent form from the attending physician, the clinical investigator or a research assistant. If a patient or his/her legal representative decides not to sign informed consent, data and samples collected for that patient will be disposed of, and patients will be excluded from analysis.

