### Study procedures

In patient with ≥2 risk factors for IAH or ACS, the intra-abdominal pressure will be measured using an intra-bladder technique. The modified Kron technique described by Cheatham and Safcsak [33] will be applied for measuring IAP. In the current study, 20 mL of saline will be used in order to comply with the current recommendations of the WSACS. For the IAP measurement, a Foley catheter will be disconnected and a 3-way-valve will be inserted to create a continuous connection to a pressure transducer (DTXPlus™ PRESS PA, reference No 686496; Argon Critical Care Systems, Singapore). For every single measurement the valve connecting the urinary drainage bag is closed and 20 mL of saline is instilled. The midaxillary line will be used as reference.

During the first 72 hours after enrolment, IAP measurement will be repeated every six hours (Table 1). At those time points (including baseline), the following samples will be collected:

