**ASSESSMENTS:**			
**Baseline variables**	X		
**Disease-related variables**	X		
**IAP measurement**		X	
**Blood sample**		X	
**Urine sample**		X	
**I-FABP measurement**		X	
**Claudin-3 measurement**		X	
**Creatinine measurement**		X	
**Treatment-related variables**		X	
**SOFA score**		X	
**Adverse events**		X	X
**Length of ICU stay**		X	X
**Mortality during ICU stay**		X	X
**Secondary interventions**		X	X

*Patients are considered eligible as soon as two IAH risk factors are present. This can either be at ICU admission or later on during ICU stay.

**Patients are followed until 72 hours or until discharge from the ICU, whichever comes first. Measurements are performed every six hours.

Urine samples for measurement of I-FABP, Claudin-3 and creatinine levels: A single fresh specimen of urine will be collected from the urinary bladder catheter that is already in situ. Samples will be kept on ice and then frozen at −80°C in aliquots within two hours of collection.Blood samples for measurement of serum I-FABP levels (NB: this only applies to patients enrolled at Erasmus MC, Rotterdam, the Netherlands): A single blood sample (10 mL) will be drawn from the arterial line that is already *in situ*. Blood will be collected in pre-chilled vacutainer containing EDTA as anticoagulent (BD Vacutainer, Becton Dickinson Diagnostics, Aalst, Belgium) and kept on ice. Blood will be centrifuged at 4°C, 4000× g for 15 minutes. Serum will be stored in aliquots at −80°C within 2 hours until analysis.

The reason for following up on patients during the first 72 hours after enrollment is based upon our observation (unpublished data) that over 95% of patients that deteriorate clinically due to increased IAP will do so during the 12–24 hours. In order not to miss any patients that may deteriorate somewhat later (*e.g.*, due to leak at the surgical site), we have set the time frame at 72 hours.

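### Enrolment may lag eligibility by up to 48 h, the sampling clock and the 12–24 h event window have no agreed origin, and the prognostic models do not separate events already present at T0

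*Protocol article*

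**What the plan says.** All references are to the protocol article, Methods/Design.

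- **Eligibility.** The first footnote to Table 1: "Patients are considered eligible as soon as two IAH risk factors are present".
- **Delay allowed.** Treatment: "Patients should be enrolled as soon as possible, but at least within 48 hours after meeting the eligibility criteria". The same section says that patients who acquire risk factors later in the stay are followed from that point.
- **Sampling clock.** Study procedures: "During the first 72 hours after enrolment, IAP measurement will be repeated every six hours", with urine (and blood at one centre) taken at the same times, baseline included. Table 1 places consent before T0 and all measurements from T0 to T72.
- **Samples before consent.** Recruitment and consent, referring to the moment two risk factors are identified: "the baseline IAP measurement and the first urine sample may have been collected prior to obtaining informed consent".
- **Reason for 72 h.** The text after Table 1 relies on unpublished data that "over 95% of patients that deteriorate clinically due to increased IAP will do so during the 12–24 hours". No origin is named. The window is then lengthened to 72 h to catch later deterioration.
- **Models.** Statistical analysis assesses the prognostic role of the markers for development of IAH, abdominal compartment syndrome (ACS), organ dysfunction or death. It uses mixed models with the biomarker as a time-dependent variable and up to 13 measurements per patient. Nothing there sets apart an outcome already present at the first measurement.

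**The concern.** The study wants a marker that rises early enough to prompt intervention. That requires a sample taken before the event. The permitted enrolment delay (48 h) is twice the outer limit of the period in which the plan expects almost all deterioration (24 h). If both run from eligibility, a late-enrolled patient can have the event first and the serial samples afterwards.

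For such a patient the odds ratio relating biomarker level to outcome describes damage already done, not prediction. The Treatment section shows why the distinction matters: it says IAH arising during the stay independently predicts mortality, while IAH present at admission does not. A T0 that floats between 0 and 48 h after eligibility mixes these two states in one model. The listed data items do not include the delay, so a reader of the results could not tell how far this had happened.

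**Working it through.** **1. The plan's own count.** 72/6 + 1 = 13 measurements, which reproduces the stated maximum. It fits a single series in which the baseline sample is T0.

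**2. The clocks side by side.**
- Study procedures starts the 72 h at enrolment.
- Table 1 puts consent before T0.
- Recruitment and consent allows the baseline IAP and first urine sample before consent.
- Treatment follows late-qualifying patients from the moment they acquire the risk factors, yet allows 48 h to enrol.

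T0 could therefore be eligibility, first sample or enrolment, and these may differ by up to 48 h.

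**3. A result needing no distribution.** Let F(d) be the share of deteriorations that occur within d hours of eligibility. If the 12–24 h runs from eligibility, F(24) exceeds 0.95. A patient enrolled at 24 h or later then has less than 5% of the deterioration risk still ahead.

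**4. Shares for shorter delays.** These need assumptions that are not in the document: the clock starts at eligibility, 95% of events are spread evenly over either 12–24 h (literal reading) or 0–24 h (looser reading), and 5% evenly over 24–72 h.

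- Literal: F(d) = 0 up to 12 h, then 0.95 × (d − 12)/12 up to 24 h.
- Looser: F(d) = 0.95 × d/24 up to 24 h.
- Both, from 24 h: F(d) = 0.95 + 0.05 × (d − 24)/48.

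| Delay | Events in 12–24 h | Events in 0–24 h |
|---|---|---|
| 12 h | 0% | 47.5% |
| 18 h | 47.5% | 71% |
| 24 h | 95% | 95% |
| 48 h | 97.5% | 97.5% |

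Half the events are passed at 12 + 12 × 0.5/0.95 = 18.3 h (literal) or 24 × 0.5/0.95 = 12.6 h (looser).

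**5. Averages over the cohort.** The document gives no delay distribution, so a range is shown.

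- Even delays over 0–48 h, literal: (12 × 0 + 12 × 0.475 + 24 × 0.9625)/48 = 60%.
- Even delays over 0–48 h, looser: (24 × 0.475 + 24 × 0.9625)/48 = 72%.
- Delays weighted towards early enrolment (exponential, cut off at 48 h), averaging F(d) over the delays:

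| Mean delay | Events in 12–24 h | Events in 0–24 h |
|---|---|---|
| about 3 h | 0.4% | 12% |
| about 6 h | 6% | 23% |
| about 11 h | 21% | 40% |
| about 16 h | 38% | 55% |

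- Clock starting at enrolment: 0% under any delay.

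**The case against.** A reader might infer that most target events will precede follow-up. The documents do not support that, for four reasons.

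- The 12–24 h has no stated origin. It is offered as the reason for a window counted from enrolment, so one clock from enrolment is a fair reading, and then nothing is lost. Against this, enrolment depends on consent and deterioration does not, and the plan's example of a late event (a surgical leak) suggests a clinical origin. The text does not settle it.
- The 48 h is a maximum, under an instruction to enrol as soon as possible. With short typical delays the loss is small.
- Larger figures come from assumed timing. An exponential onset with 95% by 24 h (rate ln 20/24 = 0.125 per hour) puts 53% of events before 6 h and 78% before 12 h. The literal wording places almost none there.
- A gap between an early baseline and a series restarting at enrolment is not stated; the count of 13 fits one continuous series.

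It is also tempting to say that early deaths are always lost or that the main comparison fails. A legal representative may consent, so the first does not follow. The IAH versus control comparison needs no sample before deterioration, and the 12–24 h figure concerns clinical deterioration, not onset of IAH.

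Finally, the handling of events present at T0 could sit in an analysis plan not shown here. That is a fair limit on the modelling part, but the conflict over the clocks is in the protocol text itself.

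What mitigates only in part: the pre-consent provision is permissive and covers one urine sample. Clinical data over the whole ICU stay can date an event but cannot supply a biomarker value from before it.

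**Conclusion.** The concern holds in limited form. The protocol permits a delay that does not fit its own event window, leaves the origin of that window unstated, and describes T0 inconsistently. If the 12–24 h runs from eligibility, patients enrolled at 24 h or later have about 95% of the deterioration risk behind them. For the cohort the share before enrolment ranges from 0% (clock from enrolment), through roughly 0–23% (mean delay 3–6 h), to 60–72% (even delays over 0–48 h). Which applies cannot be determined from the document.

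Independently of those figures, the prognostic models as described do not separate events present at T0 from events that develop later. That weakens a predictive reading of their odds ratios whatever the delay turns out to be.

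**What to change.** 1. Reconcile Treatment, Recruitment and consent, Study procedures and Table 1 on what T0 is, and state the origin of the 12–24 h.
2. Take T0 as the first baseline IAP measurement and urine sample, including one obtained before consent under the existing rule, with its disposal on refusal. Moving the whole six-hourly series, with arterial blood draws, ahead of consent would go beyond that rule and is not proposed.
3. Record the times of eligibility, T0 and onset of each event. Enrolment opened in April 2011, but for patients already included much of this should be recoverable from the routine electronic records.
4. For each outcome (IAH, ACS, new or increasing organ dysfunction, death), restrict the prognostic model to patients free of that event at T0 and use biomarker values from before the event. Because IAH requires two recordings, say how status at T0 is read.
5. Report events present at T0 separately, and show a sensitivity analysis by eligibility-to-T0 delay.

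**Cost.** Some wording, three time stamps, and fewer patients and events in the prognostic analysis, hence wider intervals there. The IAH versus control comparison and its sample size are unchanged.

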### Outcome measures

I-FABP levels will serve as primary outcome measure. Urinary and serum concentrations of I-FABP will be analyzed in duplicate using a highly specific, commercially available enzyme-linked immunosorbent assay (ELISA) that selectively detects human I-FABP (HyCult Biotechnology, Uden, The Netherlands). The ELISA will be performed following the supplier’s protocol. I-FABP levels in urine will be adjusted to urinary creatinine levels.

Claudin-3 levels will serve as secondary outcome measure. Urinary levels of Claudin-3 will be analyzed in duplicate either by ELISA (if available at time of analysis) or by Western blotting. Claudin-3 levels in urine will be adjusted to urinary creatinine levels. If analyzed from Western blots, equal amounts of each sample (adjusted to urinary creatinine levels) will be separated by sodium dodecyl sulphate polyacrylamide gel electrophoresis (SDS-PAGE), transferred to a polyvinylidene fluoride (PVDF) membrane and probed using primary antibody to Claudin-3 (Rabbit anti-claudin-3 (34–1700), Zymed Laboratories, San Francisco, CA). After incubation with goat anti rabbit HRP-conjugated secondary antibody (Jackson, West Grove, PA), a signal will be detected by supersignal west pico chemiluminescence substrate (Pierce, Etten-Leur, the Netherlands). Band intensities for each sample will be semi-quantitatively analyzed using Quantity One (Biorad, Hercules, CA). This is a straightforward approach for semi-quantitative assessment of protein levels. Urinary creatinine levels in the collected samples will be determined at the Clinical Chemistry department.

The occurrence of (increasing) organ dysfunction will be based upon the SOFA score.

### Baseline, disease and treatment-related data

In addition to the outcome variables mentioned above, the following data will be collected:

***Intrinsic variables (baseline data)***:AgeGenderWeightHeightComorbidity

***Disease-related variables at admission***:Reason of admission to the ICU (*i.e.*, type of disease or injury and type of intervention)Serum lactate concentration at baseline (sodium fluoride tube)IAP level at baselineUrinary creatinine level at baseline (sediment tube)Acute Physiology and Chronic Health Evaluation II (APACHE II) score at baseline; this is a validated and commonly applied severity of disease classification system [24]. An integer score ranging from 0 to 71 is computed based upon 12 routine physiological measurements with a higher scores implying a more severe disease and a higher risk of death.Acute Physiology and Chronic Health Evaluation IV (APACHE IV) score at baseline; this standardized scoring metrics was developed in 2005 as an improved version of the APACHE II. The previously used set of equations were re-evaluated and improved where needed. The most important change involved the new categorization of disease groups [25].Simplified Acute Physiology Score II (SAPS II) at baseline; this score was designed to measure the severity of disease for patients admitted to Intensive care units aged 15 or more [26]. The SAPS II score is calculated from 12 routine physiological measurements during the first 24 hours of ICU admission, information about previous health status and some information obtained at admission. The computed score has a range from 0 to 163 points and a predicted mortality between 0% and 100%. Higher scores imply a more severe disease and a higher risk of death.Sequential Organ Failure Assessment (SOFA) score at baseline; this score is a validated and commonly used score to track a patient’s status during the stay in an ICU. The SOFA score is a scoring system to determine the extent of a person’s organ function or rate of failure [27-31]. The score is based upon six different scores, one each for the respiratory system (*i.e.*, PaO2/FiO2 ratio), the cardiovascular system (*i.e.*, mean arterial pressure and vasopressor requirement), the hepatic system (*i.e.*, bilirubin level), the coagulation system (*i.e.*, platelet count), the renal system (*i.e.*, creatinine level or urine output), and the neurological system (*i.e.*, Glasgow Coma Score). For each of these systems, a maximum of four points can be attributed. SOFA scores are determined on a daily basis during ICU admission.

***Treatment-related variables***:Medication useInterventions performed (*i.e.*, type and number of interventions)Sequential Organ Failure Assessment (SOFA) score on day 1 to 4 (or until ICU discharge or death).Length of stay in the ICUMortality during ICU stay and during hospital stay

### Sample size calculation

In order to reliably calculate correlation coefficients for the association between IAP, I-FABP and Claudin-3 levels, at least 75 patients with IAH are needed. Malbrain *et al.* showed in a multicenter study that in a general ICU population, the prevalence of IAH (*i.e.*, IAP > 12 mmHg) and ACS (*i.e.*, IAP > 20 mmHg with concomitant new organ dysfunction) was 32%, and 4%, respectively [23]. Since we will only follow-up on patients with a minimum of two IAH/ACS risk factors, the percentage of enrolled patients that will develop IAH or ACS will be higher, and is likely to exceed 40% (unpublished data). Therefore, enrolling a total population of 200 patients will be sufficient to ascertain availability of 80 patients with IAH.

This will also be sufficient to compare I-FABP levels in patients with physiologic IAP levels with patients that developed IAH with adequate statistical power. Based upon data provided by Kanda *et al*. we expect that mean I-FABP levels will be 20.0 ± 10.0 ng/mL (range 0–100 ng/mL) in patients without IAH [32]. In patients with IAH, the I-FABP levels will be higher (≥20 ng/mL). An overall population of 200 patients (consisting of 120 controls and 80 patients with IAH) will be sufficient to detect a 0.5 SD increase to 30.0 ± 12.5 ng/mL in I-FABP level in patients with IAH (two-sided test with an α level of 0.05) with >90% statistical power.

### Recruitment and consent

Upon identification of two IAH risk factors, treatment should be initiated in compliance with international guidelines of the WSACS. This implies that the baseline IAP measurement and the first urine sample may have been collected prior to obtaining informed consent from the patient or his/her legal representative. Eligible persons admitted to the ICU who are at risk for developing IAH will be informed about the trial and asked for consent at the ICU. If patients are unconscious or otherwise not able to sign informed consent, their legal representative will be informed about the trial and asked to sign informed consent on behalf of the patient. Upon recovery the patient will be asked to sign final consent. The patient and their legal representative will receive information and a consent form from the attending physician, the clinical investigator or a research assistant. If a patient or his/her legal representative decides not to sign informed consent, data and samples collected for that patient will be disposed of, and patients will be excluded from analysis.

### Study procedures

In patient with ≥2 risk factors for IAH or ACS, the intra-abdominal pressure will be measured using an intra-bladder technique. The modified Kron technique described by Cheatham and Safcsak [33] will be applied for measuring IAP. In the current study, 20 mL of saline will be used in order to comply with the current recommendations of the WSACS. For the IAP measurement, a Foley catheter will be disconnected and a 3-way-valve will be inserted to create a continuous connection to a pressure transducer (DTXPlus™ PRESS PA, reference No 686496; Argon Critical Care Systems, Singapore). For every single measurement the valve connecting the urinary drainage bag is closed and 20 mL of saline is instilled. The midaxillary line will be used as reference.

During the first 72 hours after enrolment, IAP measurement will be repeated every six hours (Table 1). At those time points (including baseline), the following samples will be collected:

**Table 1 Tab1:** **Schedule of enrolment, interventions, and assessments**

	**Study period**		
	**Enrolment***	**Measurement ****	**Close-out**
**TIMEPOINT**	***<T*** _***0***_	***T*** _***0***_ ***to T*** _***72***_	***ICU discharge***
**ENROLMENT:**			
**Eligibility screen**	X		
**Informed Consent**	X		
**ASSESSMENTS:**			
**Baseline variables**	X		
**Disease-related variables**	X		
**IAP measurement**		X	
**Blood sample**		X	
**Urine sample**		X	
**I-FABP measurement**		X	
**Claudin-3 measurement**		X	
**Creatinine measurement**		X	
**Treatment-related variables**		X	
**SOFA score**		X	
**Adverse events**		X	X
**Length of ICU stay**		X	X
**Mortality during ICU stay**		X	X
**Secondary interventions**		X	X

*Patients are considered eligible as soon as two IAH risk factors are present. This can either be at ICU admission or later on during ICU stay.

**Patients are followed until 72 hours or until discharge from the ICU, whichever comes first. Measurements are performed every six hours.

Urine samples for measurement of I-FABP, Claudin-3 and creatinine levels: A single fresh specimen of urine will be collected from the urinary bladder catheter that is already in situ. Samples will be kept on ice and then frozen at −80°C in aliquots within two hours of collection.Blood samples for measurement of serum I-FABP levels (NB: this only applies to patients enrolled at Erasmus MC, Rotterdam, the Netherlands): A single blood sample (10 mL) will be drawn from the arterial line that is already *in situ*. Blood will be collected in pre-chilled vacutainer containing EDTA as anticoagulent (BD Vacutainer, Becton Dickinson Diagnostics, Aalst, Belgium) and kept on ice. Blood will be centrifuged at 4°C, 4000× g for 15 minutes. Serum will be stored in aliquots at −80°C within 2 hours until analysis.

The reason for following up on patients during the first 72 hours after enrollment is based upon our observation (unpublished data) that over 95% of patients that deteriorate clinically due to increased IAP will do so during the 12–24 hours. In order not to miss any patients that may deteriorate somewhat later (*e.g.*, due to leak at the surgical site), we have set the time frame at 72 hours.

In order to assess if levels of I-FABP or Claudine-3 can be used as a prognostic marker for intestinal ischemia-related morbidity it is necessary to also collect clinical data of patients during their entire stay at the ICU. These data will be extracted from the ICU patient data management system (PDMS), where they are stored as part of clinical routine. This will be done using the APACHE II, APACHE IV, SAPS II and SOFA score, which will be collected routinely for any patient admitted to the ICU. Follow-up in the ICU will include a daily physical examination, vital signs monitoring, routine blood tests, and chest radiographs or other ancillary tests as required. The attending physicians will record complications and events as well as any (secondary) intervention performed such as decompression laparotomy.

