### Biomarkers released upon loss of small intestinal integrity

Evidence is accumulating that the intestines play a central role in the origin of postoperative and posttraumatic sequelae [4-6]. Enterocyte damage and tight junction loss can be triggered by IAH, and both result in loss of intestinal integrity. As a consequence, toxins, bacteria, and undigested food particles may pass the enterocyte layer, enter the underlying vasculature, and trigger systemic inflammatory reactions that may progress to multiple organ dysfunction syndrome and even death. Peptides released upon enterocyte damage (*e.g.*, Intestinal Fatty Acid Binding protein; I-FABP) or tight junction loss (*e.g.*, Claudin-3) are potentially ideal biomarkers that will help identify patients with early IAH-induced intestinal damage.

I-FABP is a small (14–15 kDa) protein that is exclusively present in mature enterocytes of the small and large intestine. It is released into the circulation upon enterocyte membrane integrity loss and rapidly excreted into the urine (half-life 11 minutes). Elevated I-FABP levels have been found in plasma, serum, and urine in patients with intestinal ischemia, celiac disease, systemic inflammatory response syndrome and necrotizing enterocolitis [7-15]. I-FABP levels can be measured sensitively in plasma, serum, and urine using an enzyme-linked immunosorbent assay (ELISA) [7,8].

Claudins are small (22 kDa) tight junction proteins [4,16-19]. Especially Claudin-3 is expressed in high quantities solely in the intestine [18]. The amount of Claudin-3 in the intestine decreases after tight junction integrity loss [17]. Breakdown of tight junctions by loss of Claudins (as measured on Western blots in urine) is an early event in intestinal damage, resulting in intestinal barrier loss [20].

The main aim of the current study is to investigate if urinary levels of I-FABP can be used as a diagnostic tool for identifying patients at risk for IAP-related complications. Secondary aims are to determine the same for serum levels of I-FABP and for urinary and serum levels of Claudin-3.

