## Discussion

Every year, approximately 80,000 patients are admitted to an ICU in the Netherlands [34]. Specific groups of patients such as those who underwent major surgery (*e.g.*, vascular or intestinal surgery) or who sustained severe trauma are at risk of developing morbidity and mortality from postoperative or posttraumatic systemic inflammatory response syndrome, sepsis and multiple organ dysfunction. The development of such potentially lethal complications in relatively healthy surgical or trauma patients is poorly understood. Evidence is accumulating that intra-abdominal hypertension plays a central role in the origin of such postoperative and posttraumatic sequelae. An increased intra-abdominal pressure level is currently the best indicator of intra-abdominal complications. However, the IAP level does not always represent the presence or absence of organ dysfunction, substantial intra-abdominal damage may be present already prior to the development of IAH and ACS. There is a distinctive need for a non-invasive early-onset diagnostic test and biomarkers. The main aim of the current study is to test if urinary I-FABP or Claudine-3 levels can be used as diagnostic tool for identifying patients at risk for IAP-related complications. This marker can then be used in order to take the necessary clinical measures (*e.g.*, decompressive laparotomy) before the IAP has reached the level of irreversible damage to vital organs. This may prevent serious morbidity or even death in a large group patients admitted to the ICU.

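### The blood-marker aims do not match the specimens and assays described: serum Claudin-3 has no data source, EDTA plasma is called serum, the primary I-FABP specimen is not fixed, and one-centre blood sampling is not carried through

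*Protocol article*

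**What the plan says.** **Aims.** The Background (section on biomarkers of small intestinal integrity) states: "The main aim of the current study is to investigate if urinary levels of I-FABP can be used as a diagnostic tool". It continues: "Secondary aims are to determine the same for serum levels of I-FABP and for urinary and serum levels of Claudin-3". The Discussion words the main aim differently: "The main aim of the current study is to test if urinary I-FABP or Claudine-3 levels can be used as diagnostic tool".

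**Outcomes.** Outcome measures reads: "I-FABP levels will serve as primary outcome measure. Urinary and serum concentrations of I-FABP will be analyzed in duplicate". Claudin-3 is named there as the secondary outcome, and the only specimen described for it is urine: "Urinary levels of Claudin-3 will be analyzed in duplicate either by ELISA" (or by Western blot). Statistical analysis labels the I-FABP level as primary and the Claudin-3 level as secondary, without naming a specimen for either.

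**Specimens.** The abstract says that urine and serum are taken for both markers and mentions no centre restriction. Study procedures lists urine for I-FABP, Claudin-3 and creatinine, but blood for serum I-FABP alone, and adds that "this only applies to patients enrolled at Erasmus MC, Rotterdam, the Netherlands". The study has two centres. On the tube: "Blood will be collected in pre-chilled vacutainer containing EDTA as anticoagulent". After centrifugation the stored fraction is called serum. Table 1 lists the blood sample without the restriction.

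**Size.** Sample size calculation asks for at least 75 patients with IAH for the correlations. It plans 200 patients (120 controls, 80 with IAH) and claims more than 90% power at two-sided 0.05. It does not say which I-FABP specimen these figures concern.

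**The concern.** Four statements about the markers do not fit together.

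1. A secondary aim (serum Claudin-3) has no specimen and no assay assigned to it. As written it cannot be answered.
2. The blood specimen carries the wrong name. Anticoagulated, centrifuged blood yields plasma. The Background itself lists plasma and serum as separate specimen types, so the label would carry a known distinction wrongly into the report.
3. The primary outcome is not tied to one specimen. If urine and blood disagree, the text lets either stand as the primary result. There is also a practical consequence: Data monitoring checks 100% of primary-outcome data and a sample of at least 10% of the rest, so the checking of blood I-FABP depends on which section is followed.
4. The size and power statements are given for I-FABP in general, but blood is available only for the patients of one centre.

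**Working it through.** **A. The sections side by side**

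| Item | Background | Outcome measures | Study procedures | Abstract |
|---|---|---|---|---|
| Urinary I-FABP | main aim | under primary outcome | urine, both centres | collected |
| Blood I-FABP | secondary aim | under primary outcome | one centre, EDTA tube | collected, no restriction |
| Urinary Claudin-3 | secondary aim | secondary outcome | urine, both centres | collected |
| Serum Claudin-3 | secondary aim | no assay described | blood not drawn for it | collected |

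The serum Claudin-3 row is the clearest conflict. The urine line in Study procedures names Claudin-3 and the blood line beside it does not, so this is a statement of scope rather than condensation. The blood I-FABP row has two ranks. For urinary Claudin-3 the Discussion adds a third wording by placing it in the main aim.

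**B. The protocol's own figures**

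Inputs from Sample size calculation: 120 and 80 patients, 0.5 SD, two-sided 0.05.

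- Patients with IAH: 200 × 0.40 = 80.
- Power, normal approximation: z = 0.5 / √(1/120 + 1/80) = 0.5 / 0.1443 = 3.46; Φ(3.46 − 1.96) = 0.93. Noncentral t: 0.93.
- With the same section's 20.0 (SD 10.0) versus 30.0 (SD 12.5) ng/mL and unequal variances: above 0.999.

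The claim of more than 90% power reproduces for a marker measured in all 200 patients, which means urine.

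**C. Blood I-FABP**

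The share of patients at the blood-sampling centre is not stated. The shares below are assumptions, each keeping the 60:40 split of controls to IAH (normal approximation).

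| Assumed share | Controls + IAH | Power, 0.5 SD | Power, 20 vs 30 ng/mL |
|---|---|---|---|
| 90% | 108 + 72 | 0.91 | >0.99 |
| 75% | 90 + 60 | 0.85 | >0.99 |
| 50% | 60 + 40 | 0.69 (noncentral t 0.68) | 0.99 |
| 25% | 30 + 20 | 0.41 | 0.85 |

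Worked line at 50%: for 20 versus 30 ng/mL, SE = √(100/60 + 156.25/40) = 2.36; 10/2.36 = 4.24; Φ(4.24 − 1.96) = 0.99.

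The two power columns differ because the protocol's two effect wordings differ. The pooled SD is √[(119 × 100 + 79 × 156.25)/198] = 11.07, so 10 ng/mL is 10/11.07 = 0.90 SD rather than 0.5 SD.

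- For 90% power at 0.5 SD, about 106 controls are needed; 106 × (1 + 80/120) = about 177 patients at that centre.
- For 75 IAH patients with blood at 40% prevalence: 75/0.40 = 187.5, or about 188 of 200. This does not depend on the effect size.

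**D. Error rate if both I-FABP specimens were primary**

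Two tests at 0.05: 1 − 0.95² = 0.0975 if independent, and never more than 2 × 0.05 = 0.10. Positive correlation would bring it below 0.0975.

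**The case against.** The strongest defence is that the main aim is sound and much of the rest is wording.

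- **One-centre blood sampling is disclosed.** Study procedures flags it openly. A secondary marker measured at one centre still answers its aim and needs no power calculation of its own. This stands. What remains is that the abstract and Table 1 omit the restriction, and that the size section does not say its figures concern urine.
- **Outcome measures does not literally call serum I-FABP primary.** It names I-FABP and then describes the assay for both fluids. This stands too: the fault is an unfixed specimen that appears when the sections are read together, not an explicit double ranking.
- **Claudin-3 is not a rival primary.** A reader might infer from the Discussion that there are three candidate main markers, with a familywise error of 1 − 0.95³ = 14%. The documents do not support that: the Background, Outcome measures and Statistical analysis all rank Claudin-3 as secondary. The ambiguity covers two specimens of one protein. Independence is also unlikely, since the Background says that circulating I-FABP passes rapidly into urine.
- **The power loss is conditional.** A reader might conclude that blood I-FABP has only 68% power. That needs both an assumed 50% share and the 0.5 SD wording; with the protocol's ng/mL figures the same share gives about 99%.
- **The specimen label does not bias the comparison.** A reader might expect plasma values to be judged against serum reference values. No such comparison is planned; IAH and control patients are compared using the same tube.

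None of this answers the missing Claudin-3 blood assay or the wrong specimen name.

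**Conclusion.** The point holds as an inconsistency between aims, specimens and assays that should be corrected. It does not threaten the main aim.

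- Serum Claudin-3 cannot be answered as written. This rests on the text alone.
- The study's blood specimen is plasma, not serum. This is a labelling error.
- The primary I-FABP specimen is left open. Testing both as primary at 0.05 would give a familywise error of at most about 10%.
- The N of 200, the power above 90% and the 75 IAH patients can be relied on only for urine. The target of 75 with blood needs about 188 of 200 patients at one centre at 40% prevalence; the protocol expects prevalence to exceed 40%, which would lower that number.
- Power for blood I-FABP cannot be stated from the documents, because it depends on the unknown centre share and on which effect wording is meant.

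Urinary I-FABP in all 200 patients keeps its stated power (0.93 for 0.5 SD).

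**What to change.** 1. Name creatinine-adjusted urinary I-FABP as the single primary outcome in Outcome measures, Statistical analysis and the Discussion, in line with the Background.
2. Make blood I-FABP a secondary, single-centre outcome. Say in Sample size calculation that the size and power statements refer to urine.
3. Carry the one-centre restriction into the abstract and Table 1.
4. Delete the serum Claudin-3 aim from the Background and the matching words from the abstract. The alternative is to specify a validated blood assay on the stored aliquots. That is more than a text change: the only method now described is for urine, and the availability of an ELISA is uncertain.
5. Relabel only the study's own I-FABP blood specimen as EDTA plasma (abstract, Background aims, Outcome measures, Study procedures, Data collection). Leave serum lactate, which has its own sodium fluoride tube, and the literature statements on plasma and serum unchanged.

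**Cost.** With the deletion option, these are text corrections with no change to sampling. The price is one fewer secondary aim and a smaller stated N for blood I-FABP. The alternative in item 4 adds laboratory work.
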